## Coronary Angiography

The baseline, peri-, and post-procedural angiographic features will be recorded: the presence of thrombus, treatment of a non-culprit vessel during the same procedure, myocardial blush grade (MBG), thrombolysis in myocardial infarction (TIMI) flow grades, side branch occlusion, the presence of angiographically visible distal embolization, minimum lumen diameter, stent diameter, stent length, no-reflow, and slow flow. TIMI flow grades are evaluated according to the previously described method (26). The evaluation of thrombus adopts the previous evaluation standard (27). The thrombus is assessed according to TIMI thrombus classification: 0 = none, 1 = suspected thrombus, 2 = thrombus, linear size ≤ 1/2 vessel diameter, 3 = thrombus, 1/2 ≤ linear size < two times of vessel diameter, 4 = thrombus, linear size ≥ two times of vessel diameter, 5 = complete occlusion due to thrombosis. MBG’s evaluation is based on the previous description (28): 0 = no myocardial staining, 1 = slight myocardial staining, or contrast density, 2 = moderate myocardial staining or contrast density, but less than that of a contra- or ipsilateral non-infarct-related area, and 3 = normal myocardial staining or contrast density, comparable with that of a contra- or ipsilateral non-infarct-related area. Continuous myocardial staining indicates that the contrast agent leaks into the extravascular space, which is defined as grade 0. Distal embolization is defined as filling defects and/or abrupt cutoff of distal vessels in the target lesion (29). The coronary angiograms are analyzed by a physician who does not know the treatment allocation and clinical data.

## Infarct Size

The infarct size is estimated by serial monitoring of cardiac markers such as creatine kinase (CK), creatine kinase-MB (CK-MB), and troponin T. Blood samples are taken at baseline and 3, 6, 9, 12, 18, 24, and 48 h after PCI. Peak value, time to peak release as well as area under the curve are determined.

## Endpoints Assessment

The primary endpoint is to observe the probability of ST-segment resolution > 70% acquired before and 30–60 min after PPCI.

Secondary endpoints include:

1.Angiographic endpoints: TIMI flow grade, distal embolization, no reflow, slow flow, side branch occlusion, myocardial blush grade post-PPCI.2.Electrocardiographic end points: residual ST-segment deviation 30–60 min after primary PCI.3.Enzymatic infarct size.4.Mortality and Major Adverse Cardiac Events: All-cause death, cardiogenic death, cardiogenic shock, reinfarction, revascularization of target vessels, malignant arrhythmia, NYHA class IV heart failure, stent thrombosis, and myocardial infarction rehospitalization are to be registered at 30 days and 1 year.

Safety endpoints consist of in-hospital hemorrhagic and stroke complications.

Furthermore, the primary and secondary endpoints will be analyzed in a preset subgroup, which is defined as:

1.Age (<65 vs. >65 years)2.Gender3.Smoker4.Diabetes mellitus5.ST-segment resolution6.Number of diseased vessels (multi-vessel vs. single vessel)7.Proximal lesions8.Infarct-related artery [left anterior descending artery (LAD) vs. non-LAD]9.Bivalirudin10.Ischemic time (<3 vs. >3 h)11.Initial TIMI thrombus grade12.Angiographic presence of thrombus13.Intra-aortic artery balloon pump14.Left ventricular ejection fraction15.Type of P2Y12 inhibitor16.Killip class17.Symptom onset18.Pre-procedural TIMI flow19.Post-procedural TIMI flow20.Post-PCI myocardial blush grade21.Pacing use.

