## Treatment

Before PCI, ICART or thrombus aspiration is decided according to the grouping. Thrombus is aspirated by the Export aspiration catheter (Medtronic Inc., Santa Rosa, CA, United States) as previously described (24). Finally, a stent is implanted. In certain patients, pre- or postdilatation with a balloon may be necessary.

Patients are given a loading dose of aspirin (300 mg) and ticagrelor (180 mg) or clopidogrel (600 mg), and are diagnosed STEMI by electrocardiography. It’s up to the operator to decide whether to use heparin or bevaludine for anticoagulation. In the setting of STEMI, radial access is preferred. In patients with radial artery pathways, sheaths are pulled out immediately following the PCI procedure. The femoral approach is reserved for patients without the radial approach. Sheaths are exchanged immediately at the end of the PCI procedure by the Angio-Seal device (St. Jude Medical, Inc., St. Paul, MN, United States). After PCI, tirofiban is used for 36 h. Then low molecular weight heparin is given for 1–3 days after tirofiban. According to the international guidelines, standard post PCI medication includes aspirin (100 mg), ticagrelor (90 mg bid), or clopidogrel (75 mg), beta-blockers, lipid-lowering drugs, and angiotensin converting enzyme inhibitors or angiotensin II receptor blockers (8).

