### Electrocardiography

A standard 18-lead ECG is acquired at first medical contact. A standard 12 lead ECG is performed 30–60 min after PPCI. Times of symptom manifestation, arrival at the hospital, guidewire passing, thrombolysis, balloon dilatation, end of PCI, and ECG are recorded. The magnitude of ST-segment deviation is calculated 60 ms from the J-point. The ST segment of post-intervention ECG at 30–60 min is compared with that of the ECG at presentation. ST-segment elevation resolution is defined as complete (>70%), partial (30–70%), or absent (<30%) (Trials 2009, 10:90). Residual ST-segment deviation after PCI is counted as the sum of residual ST-segment depression and elevation in all leads (25). All ECG data are analyzed by a physician who is blinded to the clinical grouping and data.

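### Three of the 21 preset subgroup factors are trial outcomes: the primary endpoint variable and two secondary endpoints

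*Protocol article*

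**What the plan says.** Endpoints Assessment states the primary endpoint as follows: "The primary endpoint is to observe the probability of ST-segment resolution > 70% acquired before and 30–60 min after PPCI". Electrocardiography gives the only definition of the variable. The ECG taken 30–60 min after the intervention is compared with the one at presentation, and "ST-segment elevation resolution is defined as complete (>70%), partial (30–70%), or absent (<30"%).

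The first group of secondary endpoints is: "Angiographic endpoints: TIMI flow grade, distal embolization, no reflow, slow flow, side branch occlusion, myocardial blush grade post-PPCI".

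The same section then says that "the primary and secondary endpoints will be analyzed in a preset subgroup" and lists 21 factors. Among them are:

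- factor 5: "Diabetes mellitus5.ST-segment resolution6.Number of diseased vessels"
- factor 9: "9.Bivalirudin10.Ischemic time"
- factors 19 to 21: "Post-procedural TIMI flow20.Post-PCI myocardial blush grade21.Pacing use"

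Factor 13 is the balloon pump and factor 14 is left ventricular ejection fraction. Pre-procedural TIMI flow is listed separately, as factor 18.

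Study Design places randomisation at the decision to perform PCI. Statistical Analysis names multiple logistic regression for the primary and secondary endpoints.

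**The concern.** A subgroup analysis asks whether the treatment effect differs between kinds of patient. The factor therefore has to be fixed before treatment can act on it. Factors 5, 19 and 20 are results of the procedure, and Background and Discussion give improved perfusion and less no-reflow and slow flow as the purpose of ICART.

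Two faults follow. When an endpoint is analysed within levels of itself, nothing is left to compare. When another endpoint is analysed within levels of a variable that treatment changes, different kinds of patient are set against each other in the two arms. Such an analysis cannot say for whom ICART works, and its preset status would give a null or reversed result more credit than it deserves.

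**Working it through.** **1. Timing and role of each factor, from the text**

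| Factor | Role elsewhere in the article | Relation to randomisation |
|---|---|---|
| 5 ST-segment resolution | Primary endpoint variable (Electrocardiography, Endpoints Assessment) | After: needs the 30–60 min post-PPCI ECG |
| 19 Post-procedural TIMI flow | Secondary angiographic endpoint | After, by its name; factor 18 is the baseline version |
| 20 Post-PCI blush grade | Secondary angiographic endpoint | After, by its name |
| 9 Bivalirudin | Treatment: "It’s up to the operator to decide whether to use heparin or bevaludine for anticoagulation" | Moment of choice not stated |
| 13 Balloon pump, 21 Pacing | Not mentioned elsewhere | Not stated |
| 14 Ejection fraction | Not mentioned elsewhere | Not stated |

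**2. Primary endpoint within factor 5**

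Let Y = 1 if resolution exceeds 70%, and use the article's three levels as strata.

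- Complete stratum: P(Y = 1) = 100% with ICART and 100% with control. Difference 0.
- Partial and absent strata: P(Y = 1) = 0% and 0%. Difference 0.

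This holds whatever ICART does. Y does not vary within a stratum, so logistic regression has no estimable odds ratio. Final TIMI flow within factor 19 and blush grade within factor 20 fail in the same way.

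**3. Other endpoints within factors 5, 19 and 20**

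Two illustrations use final flow. All coefficients are assumed; none comes from the article. U is an unmeasured prognostic factor, standard normal and equal in the two arms at randomisation; T = 1 for ICART; M = 1 for good final flow.

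*(a) ICART works, entirely through flow.*
logit P(M = 1) = 0.5 + 0.8U + 0.8T
logit P(Y = 1) = −0.9 + 0.9U + 1.9M

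Integrating over U gives:

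| | Control | ICART | Difference (points) |
|---|---|---|---|
| Good final flow | 60.8% | 75.9% | +15.1 |
| ST resolution, overall | 55.1% | 61.1% | +6.0 |
| ST resolution, good flow | 74.82% | 73.17% | −1.65 |
| ST resolution, poor flow | 24.54% | 22.86% | −1.68 |

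To one decimal, the within-stratum differences are −1.6 and −1.7. Given U and M, treatment has no further effect in this model, so both come only from a shift in U. ICART moves patients of middling prognosis from poor to good flow. The mean of U therefore falls from 0.28 to 0.17 in the good-flow stratum and from −0.43 to −0.55 in the poor-flow stratum.

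*(b) ICART has no effect on ST resolution.*
logit P(M = 1) = 1.0 + 1.0T + aU
logit P(Y = 1) = 0.27 + aU

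In a simulation of 4 million patients for each value of a, the overall difference was about 0. Within strata it was:

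| a | Good flow (points) | Poor flow (points) |
|---|---|---|
| 0.5 | −0.8 | −0.9 |
| 1.0 | −2.5 | −3.1 |
| 1.5 | −4.0 | −5.0 |

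**4. What is untouched**

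The planned 286 reproduces from Sample Size Estimation. The inputs are 56.6% against 75%, two-sided 5%, 90% power, with 1:1 allocation assumed and unpooled variance.

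n per arm = (1.960 + 1.282)² × (0.566 × 0.434 + 0.75 × 0.25) / 0.184² = 134.4, so 135.
135 / 0.95 = 142.1, so 143 per arm and 286 in all.

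The sample size does not depend on any subgroup.

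**The case against.** The main argument on the other side is that little rests on the subgroups. The sample size and the main comparison stand if every subgroup row is ignored. That is right, and it limits the severity.

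The degenerate result is also narrow. It concerns an endpoint analysed within its own levels. One-year events by ST-resolution stratum, for example, can be computed. This stands too, but such a comparison conditions on an outcome and is not a randomised one.

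Factor 5 might be meant as spontaneous resolution before the procedure. The article describes no second ECG before PCI and gives no other definition, so the text does not support that reading.

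The models are invented, and model (a) assumes that ICART acts only through flow, so the loss of effect within strata is built in. They show direction, not the size of bias in this trial.

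A reader might go further in two ways that the article does not support:

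- **Treatment factors and ejection fraction.** One might infer that bivalirudin, balloon pump, pacing and ejection fraction are invalid too. No section gives their timing. The exclusion of cardiogenic shock makes balloon pump use before randomisation less likely but does not settle it. The operator's choice of anticoagulant in an open-label trial is a reason for care, but the article does not say when it is made. P2Y12 loading is tied to the diagnosis of STEMI and may come before randomisation.
- **Multiplicity.** One might compute a high chance of a false positive over 21 independent tests at 5%. The factors plainly overlap (thrombus grade and presence of thrombus, for example), and one is not estimable for the primary endpoint. Interaction tests, multiplicity and exploratory labelling are commonly left to an analysis plan, which is not at hand.

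**Conclusion.** The point holds for factors 5, 19 and 20, and it rests on the article's own definitions and its time of randomisation. The primary endpoint within factor 5, split at 70%, has a difference of exactly zero by construction and no estimable odds ratio; this needs no assumption. For other comparisons within the three factors, bias arises if treatment changes the factor and some prognostic variable drives both factor and endpoint. The first is the trial's hypothesis and the second is to be expected in STEMI. The size is unknown. In the assumed models the distortion ran from under 1 point to about 5 points, and in one of them it turned a 6.0-point benefit into a small apparent harm in both strata.

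This should be fixed, but it does not threaten the trial's main answer. For bivalirudin, balloon pump, pacing and ejection fraction, the most that can be said is that their timing has to be settled before they are used as subgroup factors.

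**What to change.** Delete factors 5 (ST-segment resolution), 19 (post-procedural TIMI flow) and 20 (post-PCI blush grade) from the subgroup list. Report them only as outcomes by arm, which the plan already provides for.

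Add one sentence: bivalirudin, balloon pump, pacing and left ventricular ejection fraction are used as subgroup factors only by status recorded before randomisation, and are otherwise described by arm.

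The cost is three list entries, one sentence and a shorter subgroup table. No patient, measurement or change to the primary analysis is needed. The article gives the trial as still recruiting, and Data Collection and Management already says how changes of plan are communicated.

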## Clinical Follow-Up

All-cause death, cardiogenic death, cardiogenic shock, reinfarction, revascularization of target vessels, stroke, malignant arrhythmia, NYHA class IV heart failure, bleeding complications, stent thrombosis, and myocardial infarction rehospitalization are to be registered at 30 days and 1 year. The follow-up information will be obtained from hospital records as well as by telephone follow-up with the patients and/or their relatives.

## Data Collection and Management

Data and instrumental measurements will be collected from all subjects using an electronic data capture system (EmpowerEDC, Shanghai, China). Data entry and management will be completed by an independent data administrator to guarantee data accuracy. Only the principal investigator could access the data. The final dataset can be acquired only by the principal investigator and the independent statistician. All procedures will comply with the confidentiality standards for medical data. All documents related to clinical trial implementation will be retained by the principal investigator. Important scheme modifications during this project will be communicated to the institutional review board, trial registry, investigators, trial participants, and the journal of publication. Management and analysis of data will be carried out by an independent expert statistician.

## Statistical Considerations

### Sample Size Estimation

It has been reported that the incidence of ST-segment elevation resolution >70% has been reported to be 56.6% in STEMI patients treated with thrombus aspiration (24). We hypothesize that ICART administration during PCI increases the incidence of ST-segment elevation resolution >70–75%. To detect this difference between ICART and thrombus aspiration or PTCA groups, 286 patients are required to reach a 5% significance level (two-sided) with 90% power, which allows 5% of cases to fall off.

### Statistical Analysis

Statistical analysis will be carried out using the SPSS statistical software package (version 18.0; SPSS, Inc., Chicago, IL, United States), and the level of significant difference will be established at α = 0.05. The data analysis will be performed by an independent professional statistician who is blinded to allocation. Analysis of efficacy will include all participants who complete the whole study.

Descriptive statistics will be used to compare the baseline characters between ICART and thrombus aspiration or PTCA group. If the normality test is satisfied, the independent *t*-test will be used; otherwise, the Mann-Whitney U test will be carried out. Regarding the primary and secondary endpoint measures, multiple logistic regression will be used to compare the differences. The mean and standard deviation values of these parameters will be reported.

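### The efficacy analysis is limited to patients who complete the whole study, although the primary endpoint is read within an hour of PCI and death up to 1 year is itself an endpoint

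*Protocol article*

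**What the plan says.** The Statistical Analysis section defines one efficacy population: "Analysis of efficacy will include all participants who complete the whole study". The article names no intention-to-treat or other all-randomised set, and gives no separate set for the primary endpoint.

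The other relevant statements are these:

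- **Randomisation** takes place when PCI is decided on (Study Design).
- **Primary endpoint:** "ST-segment resolution > 70% acquired before and 30–60 min after PPCI" (Endpoints Assessment). The Electrocardiography section agrees: "A standard 12 lead ECG is performed 30–60 min after PPCI".
- **Secondary endpoints** include "Mortality and Major Adverse Cardiac Events: All-cause death, cardiogenic death, cardiogenic shock, reinfarction, revascularization of target vessels" (Endpoints Assessment).
- **Length of follow-up:** events up to and including "stent thrombosis, and myocardial infarction rehospitalization are to be registered at 30 days and 1 year" (Clinical Follow-Up). Information comes from hospital records and from telephone contact with patients or relatives.
- **Sample size:** 286 patients, "which allows 5% of cases to fall off" (Sample Size Estimation).
- **Design:** open-label with blinded endpoint evaluation (Abstract, Methods/Design).

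**The concern.** The primary outcome is known within about an hour of the procedure, but under the stated rule a patient's place in the primary analysis depends on what happens over the following year. A patient with a readable ECG who is lost or dies at month 6 would be removed from a comparison to which that patient has already contributed a complete result.

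This has two consequences. First, the primary comparison is no longer between the groups as randomised. If later death or loss is related both to the arm and to the ECG result, the completer comparison is biased. Because the trial is open-label, withdrawal may differ by arm, and blinded ECG reading does not prevent that. Second, a patient who dies before 1 year would not ordinarily be said to have completed the study, so the rule would remove the deaths that the mortality endpoint is there to count.

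This is a rule that the protocol states, not a detail left to a later document. A statistical analysis plan that followed it would inherit the problem, and one that analysed all randomised patients would contradict it.

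**Working it through.** **Inputs.** From Sample Size Estimation: control rate 56.6%, two-sided 5% level, 90% power, 5% loss, 286 patients in total. Two inputs are assumptions. The ICART rate is taken as 75%, because the printed hypothesis is worded ambiguously. Allocation is taken as 1:1 (143 per arm), because no ratio is printed. The article gives no rates of death or loss by arm, so every non-completion figure below except the 5% is assumed.

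**1. The plan's own figure.** Write p₁ = 0.566, p₂ = 0.75, p̄ = 0.658.

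- Pooled variance: n = [1.96·√(2·0.658·0.342) + 1.2816·√(0.566·0.434 + 0.75·0.25)]² / 0.184² = 137.6, so 138 per arm and 276 in total; 276/0.95 = 290.5, so 291.
- Unpooled variance: n = (1.96 + 1.2816)²·(0.2456 + 0.1875)/0.184² = 134.4, so 135 per arm and 270 in total; 270/0.95 = 284.2, so 285.

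The printed 286 lies between the two. The sample size is not in error.

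**2. Power under the two populations** (75% vs 56.6%).

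| Analysed | Power |
|---|---|
| All 286 randomised | 91.1% |
| Completers at the planned 5% loss (about 272) | 89.7% |
| Completers at an assumed 10% loss | 88.0% |
| Completers at an assumed 15% loss | 86.1% |

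**3. Bias with no true effect.** Let both arms truly resolve at 56.6%. If a fraction d of an arm does not complete, and these patients resolve at rate r, the rate among completers is (0.566 − d·r)/(1 − d). Take d = 10% in one arm and 5% in the other, with the same r in both. Type I error is the exact binomial rejection probability of the pooled z-test with 129 and 136 completers (143 × 0.90 and 143 × 0.95, rounded).

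| r among non-completers | Arm with 10% loss | Arm with 5% loss | False difference | Type I error |
|---|---|---|---|---|
| 56.6% | 56.6% | 56.6% | 0 | about 5% |
| 40% | 58.4% | 57.5% | 1.0 points | 5.5% |
| 20% | 60.7% | 58.5% | 2.1 points | 6.6% |
| 0% | 62.9% | 59.6% | 3.3 points | 8.7% |

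Example for r = 20%: (0.566 − 0.10·0.20)/0.90 = 0.607 and (0.566 − 0.05·0.20)/0.95 = 0.585.

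The false difference favours the arm that loses more patients, so it can run either way. With 5% loss in both arms and the same r, there is no false difference. Both rates rise together, for example to 58.5% at r = 20%.

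**4. Mortality endpoints.** No arithmetic applies. The efficacy rule keeps those who complete the study, the endpoint list includes all-cause death to 1 year, and nothing in the article says that a patient whose death is recorded has completed.

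**The case against.** The strongest defence is that completing the whole study is not defined. Follow-up uses hospital records and relatives as well as patients, so it is set up to learn of deaths, and the sponsor may regard a patient with a registered death as complete. That is possible, and for this reason it would go too far to say that deaths are excluded by construction. But the article does not say it. Even on that lenient reading, a patient lost after a valid ECG still leaves the primary analysis.

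A second objection is that bias is not shown, and this stands in part. A reader might infer that the rule necessarily inflates the resolution rate or favours one arm. It does so only if non-completers resolve less often than completers, and a difference between arms also needs loss, or the prognosis of those lost, to differ by arm. The documents give no data on either. Zero resolution among non-completers is an extreme assumption, especially for patients lost late for administrative reasons.

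A reader might also infer that patients who cross over, or whose procedure is not finished, are dropped. The text does not support this. The rule refers to completing the study, not to treatment received, and such a patient followed to 1 year would be included.

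Finally, the plan budgets for 5% loss, and power at that loss is 89.7% against a target of 90%. Power is therefore not the reason to change the rule.

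**Conclusion.** The point holds and must be fixed. As written, the efficacy analysis makes a 30–60 min endpoint depend on 1-year completion. On its ordinary reading it also removes early deaths from the endpoints that count them.

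The document does not allow the bias to be sized. With no true effect and an assumed 10% vs 5% non-completion, the false difference runs from 0 to 3.3 points and type I error from about 5% to 8.7%. The top of that range requires that no non-completer resolved. The middle of it (20–40% resolution) gives 1.0–2.1 points and 5.5–6.6%. These figures rest on 143 per arm, on unequal loss, and on the same resolution rate among non-completers in both arms. Equal loss with equal prognosis gives no false difference.

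The case for change does not depend on any one of these figures. The rule discards primary data already in hand and gives up the protection of randomisation for no gain.

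**What to change.** Replace the sentence in Statistical Analysis with:

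> Efficacy will be analysed in all randomised patients in the arm to which they were assigned, regardless of completion of follow-up. Patients who die before the 30–60 min ECG count as not achieving >70% resolution. Deaths count as events in the 30-day and 1-year endpoints.

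Add a prespecified rule for other missing or unreadable ECGs; the choice of method can be left to the statistical analysis plan. Keep the completer analysis as a sensitivity analysis only. Wording about censoring patients at last contact is needed only if a time-to-event analysis is specified, since the article plans logistic regression for the primary and secondary endpoints.

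The cost is a few lines of text. The sample size stays at 286, and no extra patients, visits or measurements are needed. The change should be made and dated before the data are analysed, because in an open-label trial a population chosen afterwards would carry little weight.

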**Methods/Design:**

IntraCoronary Artery Retrograde Thrombolysis (ICART) vs. thrombus aspiration or PTCA in STEMI trial is a single-center, prospective, randomized open-label trial with blinded evaluation of endpoints. A total of 286 patients with STEMI undergoing PPCI are randomly assigned to two groups: ICART and thrombus aspiration or PTCA. The primary endpoint is the incidence of >70% ST-segment elevation resolution. Secondary outcomes include distal embolization, myocardial blush grade, thrombolysis in myocardial infarction (TIMI) flow grade, and in-hospital bleeding.

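### Logistic regression with means and SDs is set for all primary and secondary endpoints, which does not fit the continuous secondary endpoints, and mean and SD misdescribe the binary and graded ones

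*Protocol article*

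**What the plan says.** The Statistical Analysis section of the protocol article names one model and one summary for the primary and secondary endpoints together: "multiple logistic regression will be used to compare the differences. The mean and standard deviation values of these parameters will be reported". The sentences just before it deal with baseline characteristics and give a t-test or a Mann-Whitney test, depending on a normality check.

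The endpoints under that rule are of several types:

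- **Primary:** ST-segment resolution above 70%, yes or no (Endpoints Assessment).
- **Electrocardiographic secondary:** "residual ST-segment deviation 30–60 min after primary PCI", which the Electrocardiography section defines as a sum over all leads.
- **Enzymatic infarct size:** serial CK, CK-MB and troponin T, from which "Peak value, time to peak release as well as area under the curve are determined" (Infarct Size).
- **Angiographic secondary:** TIMI flow grade and myocardial blush grade, which are graded, plus yes/no findings such as distal embolization.
- **Death and major adverse cardiac events:** registered at 30 days and at 1 year.

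In-hospital bleeding and stroke are listed separately as safety endpoints, and the model sentence does not name them.

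**The concern.** Logistic regression models a categorical outcome. A sum of ST deviation, an enzyme peak, a time to peak and an area under the curve are measured quantities. Following the sentence literally means dichotomising each of them, and no threshold is given. That discards information and leaves the result dependent on a threshold still to be chosen. An analysis plan written to match the sentence would inherit the problem, and one that used a suitable model would depart from the published protocol.

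The summary has the opposite fault. Mean and SD can describe a continuous measurement, but they are not how a yes/no endpoint, a four-level grade or an event should be reported. Readers need the count and percentage in each arm.

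**Working it through.** **1. Match of method to endpoint**

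| Endpoint | Type | Logistic regression as written | Mean and SD |
|---|---|---|---|
| ST resolution >70% (primary) | binary | valid | wrong; n (%) needed |
| Residual ST deviation | continuous | only after a cut-point, none given | acceptable unless skewed |
| Enzyme peak, time to peak, AUC | continuous | only after a cut-point, none given | acceptable unless skewed |
| TIMI flow, blush grade | ordinal | usable in ordinal form; form not stated | wrong; n (%) per grade |
| Distal embolization, no reflow, slow flow, side branch occlusion | binary | valid | wrong; n (%) |
| Death and MACE at 30 days and 1 year | events at fixed times | usable as fixed-time yes/no | wrong; n (%) |

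The model fails for rows two and three, which are two of the four numbered secondary groups in Endpoints Assessment. The summary fails for the other four rows.

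**2. Mean and SD for the primary endpoint**

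For a 0/1 variable the mean is the proportion p and the SD is √[p(1−p)]. At p = 0.75 the SD is √0.1875 = 0.433. At p = 0.566 it is √0.2456 = 0.496. The SD is fixed by p and tells the reader nothing further.

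**3. Does the logistic model harm the primary comparison?**

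Inputs from Sample Size Estimation:

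- Control rate: "56.6% in STEMI patients treated with thrombus aspiration".
- ICART rate: the wording is "ICART administration during PCI increases the incidence of ST-segment elevation resolution >70–75", read here as a rise to 75%. This reading is an assumption, but a 70% target does not reproduce the stated total (540 before loss, 570 after, pooled formula).
- Error rates: "286 patients are required to reach a 5% significance level (two-sided) with 90% power".
- Loss: "which allows 5% of cases to fall off".
- Allocation: 1:1 is assumed, because the abstract says only "randomly assigned to two groups: ICART and thrombus aspiration or PTCA".

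The plan's own figure comes first, using the unpooled formula for two proportions:

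n = [p₁(1−p₁) + p₂(1−p₂)] × (z₀.₉₇₅ + z₀.₉₀)² / (p₂ − p₁)²

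= (0.2456 + 0.1875) × (1.960 + 1.282)² / 0.184² = 134.4, so 135 per arm.

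Allowing for 5% loss, 135/0.95 = 142.1, so 143 per arm and 286 in total. The stated figure is reproduced exactly.

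Next, the logistic (log odds ratio, Wald) test at the same rates:

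- OR = (0.75/0.25)/(0.566/0.434) = 2.30, and its log is 0.833.
- Variance per patient per arm = 1/0.1875 + 1/0.2456 = 9.40.
- n for 90% power = 9.40 × 10.51 / 0.833² = 142.4, so 143 per arm (286) before loss, or 302 with 5% loss.
- Power with 135 per arm: SE = √(9.40/135) = 0.264; 0.833/0.264 − 1.960 = 1.196; power 88.4%.
- Power with 143 per arm: 90.1%.

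The unpooled test of the difference in proportions has 90.1% power with 135 per arm. The logistic test therefore costs about 1.7 points of power if the full 5% is lost.

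**4. Effect scale at the design rates**

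The same contrast is a risk difference of 75 − 56.6 = 18.4 points, a risk ratio of 0.75/0.566 = 1.33, and an odds ratio of 2.30. The odds ratio is correct, but because the outcome is common a reader could take it for more than a doubling of the chance of resolution.

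**The case against.** The strongest reply is that logistic regression is a standard model for the binary primary endpoint, and that the rest is loose wording in a condensed article. Much of this stands, and it rules out several stronger readings.

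- **A reader might infer that the primary analysis contradicts the sample size.** It does not. The two tests address the same null hypothesis with nearly equal power, and the article never commits to the risk difference as the effect to be reported. Adding it is a reporting improvement.
- **A reader might infer that graded and event endpoints cannot be analysed this way.** The text says multiple logistic regression, not binary. Ordinal logistic regression suits TIMI flow and blush grade. Events registered at 30 days and 1 year can be analysed as yes/no outcomes at those times. This gives up timing and handles incomplete follow-up poorly, but it is workable. The efficacy set of completers is a separate question.
- **A reader might infer that cut-points must be post hoc.** An analysis plan that is not shown could fix them in advance. The article is at fault only for assigning a model that needs them.
- **A reader might put a figure on the lost information**, such as the 2/π (about 64%) efficiency of a median split of a normal variable. The plan proposes no median split and the documents say nothing about the distributions, so that figure does not describe this trial.

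It can also be argued that the t-test and Mann-Whitney rule covers all continuous data, and that the mean and SD sentence is meant only for continuous measures. The first sentence names no variable, so this is possible. By position, though, it belongs to the baseline comparison. The endpoint sentence then opens a new topic and names logistic regression alone, and the mean and SD sentence refers back to those same endpoints. The likelier reading leaves the defect in place, and the other still calls for clearer wording.

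**Conclusion.** The point holds in a limited form. As written, the method is wrong for residual ST-segment deviation and for enzyme peak, time to peak and AUC. The summary is wrong for the binary primary endpoint and for graded and event endpoints. This is a stated misassignment, not a detail left to an analysis plan.

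The severity is moderate. It affects the analysis of two secondary endpoint groups and the way results are reported. The primary hypothesis test and the total of 286 stand, assuming a 75% target and 1:1 allocation. How much information dichotomising would lose cannot be sized from the documents, because neither thresholds nor distributions are given.

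**What to change.** Replace the single sentence with a method and a summary for each endpoint type, settled before unblinding:

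- **Primary:** keep logistic regression. Report n (%) per arm and the odds ratio, preferably with a risk difference and 95% CI alongside.
- **Enzyme peak and AUC:** linear model, on the log scale if skewed.
- **Time to peak and residual ST deviation:** linear or rank-based model.
- **Continuous summaries:** mean and SD, or median and IQR where skewed.
- **TIMI flow and blush grade:** state that ordinal (proportional-odds) logistic regression is used, with n (%) per grade.
- **30-day and 1-year events:** n (%) and fixed-time binary analysis. Time-to-event methods are an option only if event dates are recorded, which the article does not say; it gives only the two registration times.

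The cost is analysis wording and modest programming. Sample size and trial conduct do not change, and no new data are needed unless the time-to-event option is chosen and dates are not already captured.
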